## Abstract

**Introduction:**

The health benefits of physical activity are well established; however, most older people are not sufficiently physically active. Despite the availability of various physical activity interventions and programs, implementation of effective prevention strategies to reduce older people’s physical inactivity are lacking. The ENJOY IMP-ACT project is an implementation research project, based on a previous evidence-based physical and social activity program utilising specialised outdoor exercise equipment (the Seniors Exercise Park) for older people. The ENJOY IMP-ACT aims to increase participation in physical activity to improve health outcomes for older people in Victoria, Australia.

**Method:**

The ENJOY IMP-ACT is a hybrid II implementation-effectiveness pre-post mixed method study design. Five local governments (6 public sites/parks) will undergo a 3-month control period followed by 9-months implementation intervention (TERM framework intervention: Training, Engagement, Resources development, Marketing and promotion), and a maintenance phase (3 months). Various methodologies will be employed throughout the project at each site and will include direct observations of park users, intercept surveys with park users, online access monitor platform (using an online app), interviews with stakeholders and exercise program leaders, a process evaluation of physical activity programs, a social return-on-investment analysis, and other related activities.

**Discussion:**

Through the implementation framework design, the ENJOY IMP-ACT is uniquely placed to translate an evidenced-based physical and social activity program into real world settings and increase physical activity among older people. If successful, this program will inform scale up across Australia with the goal of improving the health and wellbeing of older people.

**Trial registration:**

This registration trial is prospectively registered with the Australian New Zealand Clinical Trials Registry. Trial number ACTRN12622001256763. Date registered 20/09/2022.

## Background

Higher sedentary behaviour and physical inactivity are strongly associated with all-cause mortality, increased chronic disease, age-related multi-morbidity, functional dependence, and poorer mental health outcomes in older age [1–3]. Physical inactivity costs health-care systems over $53.8 billion (INT$) annually worldwide [4]. An adequate level of physical activity is known to reduce the risk of health problems in older people [5–7] and can also prevent or ameliorate age-related multi-morbidity [3]. Yet only 25% of older Australians meet the recommended physical activity guidelines [8]. Green space, parks and outdoor leisure are essential for our mental and physical health, as they play an important role in increasing engagement in physical activity [9, 10]. Furthermore, the health benefits of outdoor spaces and parks for older people in particular are also well known [11].

Despite evidence demonstrating the importance of physical activity, the participation of older populations in physical activity programs is low [12]. Effectively translating and sustaining programs in real world settings is a complicated and lengthy process [13]. Few evidence-based physical activity interventions have been effectively implemented into real-world settings [14]. Hence a priority is to identify programs that can be scaled up, understand factors affecting implementation, and establish a framework to guide successful research translation and program sustainability [13]. We previously developed the Seniors Exercise Park program, an innovative outdoors exercise program using specialised outdoor exercise equipment, designed to promote community health and wellbeing through the provision of a unique exercise and social support program. We have demonstrated the effectiveness of the Seniors Exercise Park program in a randomised controlled trial [15, 16] and a community translation research project (ENJOY project) [17]. The ENJOY project provided further evidence that our program promotes sustained engagement of older people in physical activity, in addition to improving physical function, wellbeing, quality of life, and reduced risk of falls [17, 18]. The social aspects and the perceived health benefits (e.g., better health, improved balance, strength, mobility) were key facilitators of ongoing participation [19]. Our work with communities and local governments highlights the potential of this innovative approach to improve older people’s lives through changes in the built environment [20]. Participation in the program is also likely to reduce social and health-care costs [21]. Through our ongoing work with local governments, we have developed a framework to build capacity and knowledge in the community for sustainable impact with the aim of increasing older people’s park visitation and physical activity [22]. Consequently, the next stage is to scale up this innovative approach across additional local governments (municipalities) in Victoria, Australia (including regional areas) and evaluate the process of translating this project across the community and assessing its impact at a larger scale.

The aims of the present study, the ENJOY Seniors Exercise Park IMP-ACT project (ENJOY IMP-ACT: IMProving older people’s health through physical ACTivity), are to evaluate: (1) the effectiveness of the implementation framework on increasing uptake and usage of the Seniors Exercise Park across six local areas and (2) the impact of the ENJOY Seniors Exercise Park on older people’s physical activity and wellbeing, and (3) the social return-on-investment (SROI).

## Methodology

### Study objectives

Aim 1 – to evaluate the effectiveness of the implementation framework on increasing uptake and usage of the Seniors Exercise Park across six sites within five local government regions. Specifically, we will evaluate:
the number of older people engaged in physical activity utilising the Seniors Exercise Parksthe types of usage and uptake (e.g., organised programs, independent usage)the contexts and mechanisms (barriers/facilitators) influencing implementation.Aim 2 – to improve physical activity and wellbeing of older people using the equipment. Specifically, we will evaluate:the physical activity and wellbeing outcomes of older people utilising the equipmentolder people’s usage characteristics of the equipment (e.g., frequency, duration).Aim 3 – to evaluate the social return-on-investment when scaling the Seniors Exercise Park across multiple local government areas.

### Study design

All procedures involved in this trial will be conducted in compliance with the National Statement on Ethical Conduct in Human Research and the Australian Code for the Responsible Conduct of Research. The study was approved by the Monash University Human Research Ethics Committee, Melbourne Australia (Project ID: 35502). The study was designed according to the Strengthening The Reporting of Observational studies in Epidemiology (STROBE) statement [23]. STROBE check list is provided as an additional file.

The ENJOY IMP-ACT study is an implementation research project employing a hybrid II implementation-effectiveness pre-post mixed method design [24]. We will implement and evaluate the implementation intervention, process and impact using the Reach, Effectiveness, Adoption, Implementation, and Maintenance (RE-AIM) Framework [25] and our adopted logic model (see Fig. 1). Six sites in Victoria, including two regional sites, will participate in the study with a pragmatic staggered commencement. Each site will have a 3-month control period followed by 9-months implementation intervention (TERM framework intervention: Training, Engagement, Resources development, Marketing and promotion), and a maintenance phase (3 months) (Fig. 2). The pre-post design is a pragmatic real-world design where all local governments will receive the implementation intervention framework. A control period will act as the waiting list ‘control arm’.

**Fig. 1 Fig1:**
[figure not shown]
The ENJOY IMP-ACT implementation activities, process and impact evaluation using the RE-AIM Framework and study-specific adopted logic model

**Fig. 2 Fig2:**
[figure not shown]
Project’s phases at each site

To address the study aims, multiple methodologies will be employed, including: direct observations of park users, intercept surveys with park users, online access monitoring platform (using an online mobile application), interviews/surveys with stakeholders and exercise program leaders, and process evaluation (review/audits of physical activity programs and other related activities).

#### Study setting and partners

In this study, five councils (six parks/sites) will participate in the project (four in metropolitan Melbourne and one in regional Victoria, Australia), including: City of Whittlesea (metropolitan), Nillumbik Shire Council (metropolitan), Hobsons Bay City Council (metropolitan), Wyndham City Council (metropolitan), and Mitchell Shire Council (two sites in regional Victoria). The proportion of the older population among these five local government ranges between 10.9% to 22% (people 60 years and over) and 7.4% to 17% (people 65 years and over) [26].

The design of the project aims for implementation in staggered stages of commencement in the following order: Barry Rd, Thomastown (City of Whittlesea); Andrew Pocket Park, Eltham (Nillumbik Shire Council); Donald Mclean Reserve, Spotswood (Hobsons Bay City Council); Central Park, Hoppers Crossing (Wyndham City Council); The Elms Reserve, Kilmore; and Chittick Park, Seymour (Mitchell Shire Council). Details of each park location, features and the surrounding areas are provided in Table 1. The locations of the metropolitan parks are spread as follows: 15–20 km north and north-east of the Melbourne Central Business District (CBD) (Thomastown and Eltham), 7 km south-west of Melbourne's CBD (Spotswood) and 24 km south-west of Melbourne's CBD (Hoppers Crossing). The two regional sites are located 65-104 km north of Melbourne (Kilmore and Seymour respectively).

**Table 1 Tab1:** Parks amenities and features

Amenities /features	Barry Road Community Activity Centre, Thomastown	Park Andrew Pocket Park, Eltham	Donald Mclean Reserve, Spotswood	Central Park Community Centre, Hoppers Crossing	The Elms Reserve, Kilmore	Chittick Park, Seymour
Within Seniors Exercise Park area						
Seniors Exercise Park equipment	Yes	Yes	Yes	Yes	Yes	Yes
Table and seats	2 benches, 1 × picnic table with chairs	2 benches, 1 × picnic table with chairs	1 bench	2 benches, 1 × picnic table with chairs	1 bench, 2 × picnic tables with chairs	2 benches
Shade Sail	Yes	Yes	No	Yes	No	No
Surrounding area adjacent to the Seniors Exercise Park						
Sport play court/field (e.g. oval/basketball/tennis court/netball)	Tennis court	Tennis court, mini-basketball court	Football oval	Pétanque	No	Football ovals
Water fountain	No	Yes	Yes	No	No	Yes
Public Toilet	No	Yes	Yes	No	No	No
BBQ / Picnic area	Yes	Yes	Yes	Yes	Yes	Yes
Seated benches	Yes	Yes	Yes	Yes	Yes	Yes
Roofed shaded area	Over picnic table	Over picnic table	Over picnic table	No	Over picnic table	Over picnic table
Kids playground / play space	1–2	1–2	≥ 2	≥ 2	1–2	≥ 2
Sand pit	No	No	Yes	No	No	Yes
Table and seats	Yes	Yes	Yes	Yes	No	Yes
Other Exercise equipment	No	No	Yes	No	No	No
Walking track	No	Yes	Yes	Yes	Yes	No
Garden beds and landscaping	Yes	Yes	Yes	Yes	No	Yes
Trees	Yes	Yes	Yes	Yes	Yes	Yes
Dog area (off leash/fenced area)	No	No	Yes	No	No	No
Buildings/facility centres	Community centre	Tennis club	Football clubhouse	Community centre	No	Concert band hall
Parking Facilities	Yes	Yes	Yes	Yes	No (only residential street parking)	Yes

Each participating council has installed the Seniors Exercise Park and the site is open to the public (Fig. 3). Key staff from each councils’ Positive Ageing/Community Development team (or equivalent) and Open plan/Landscape team (or equivalent) will work closely with the research team to assist with the delivery of the project and to facilitate data collection. A formal agreement (e.g., Memorandum of Understanding (MOU)) will be signed off between the research organisation and each local government prior to commencement of data collection.

**Fig. 3 Fig3:**
[figure not shown]
The Seniors Exercise Park in Andrew Pocket Park, Eltham, Melbourne

Variation in the project’s timeline may occur with potential delays due to weather conditions, future COVID-19 or similar restrictions, local government internal processes, and public holidays. A suitable timeline for the project’s execution and associated data collection will be developed incorporating a contingency plan into the timeline in the study design to account for potential impact of factors outside the researchers’ control (e.g., weather, site refurbishment) which are frequently experienced in natural experiments and pragmatic trials such as this [27, 28].

### Study population

#### Recruitment

Older people visiting the participating parks are potential participants for the intercept surveys and will be recruited at the sites. Information about the study will be provided to residents/visitors via verbal communication as well as via hard copies of the information sheet.

Leaders of delivery programs (seniors group leaders, allied health professionals, exercise instructors), and key stakeholder representatives (council staff, community health/leisure centre managers/coordinators) will be recruited to participate in an interview/survey for the process evaluation.

#### Inclusion criteria

For the observational data collection, all park visitors during park observation periods will be included in the data recording.

For the face-to-face intercept survey at the park during the park observation periods, the following inclusion criteria will be applied: (1) adults aged 60 and over, (2) adults who are able to understand basic English and have conversational English.

For the semi-structured interviews for the contextual factors influencing the implementation, the following inclusion criteria will be applied: (1) key stakeholder representatives—council staff within the division (or equivalent) that are responsible or involved with the Seniors Exercise Park management/coordination/activation; community health/leisure centre managers/coordinators within the participating municipalities; (2) leaders of delivery programs (seniors group leaders, allied health professionals, exercise instructors) who utilise the Seniors Exercise Park as part of their program/service delivery.

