#### Exclusion criteria

The following exclusion criteria will be applied for the face-to-face intercept surveys at the park: (1) participants who identify themselves as less than 60 years of age and (2) who are unable to understand basic conversational English.

The following exclusion criteria will be applied for the key stakeholder representatives and leaders of delivery programs interviews: staff that are not directly involved with the management or activation of the Seniors Exercise Park or people who do not deliver/run programs/services using the outdoor equipment.

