##### Intercept surveys

Each site will have a 3-month control period followed by a 9-month implementation intervention period (TERM—Training, Engagement, Resources development, Marketing and promotion), and a maintenance phase (3 months). Evaluation (observation of users/visitors and onsite intercept surveys) will take place each month during the control period (baseline = B), every 3 months during implementation intervention phase (I1, I2, I3), and once during the maintenance phase (M1), see Table 2 and Fig. 2. The control period will include three evaluation points (B1, B2, B3), each occurring over a 10-day period per month (including one weekend). The time series evaluation will enable controlling for variations in equipment access due to weather (seasonal effects). Potential participants (park users in the specified target area) will be approached by trained, clearly identifiable research staff to see if they meet inclusion criteria. They will be provided with a verbal explanation about the study and all ethical considerations and invited to participate in a survey. Interested participants will then be asked to provide a verbal agreement (consent) to participate. Upon verbal consent, a paper survey will be administered by the researcher onsite. If more than one person is in the park during any observation period, the research staff decision of who to approach would be guided by aiming to overall recruit an equal number of men and women. The participants will be eligible to complete only one intercept survey during the baseline and maintenance period. During the intervention period the same participants can be surveyed multiple times.

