### Assessments

#### Outcome measures

##### Primary outcomes

The primary impact measures of the implementation framework intervention are: (1) *the number of older people* who engage in physical activity using the Seniors Exercise Park (irrespective of usage mode: e.g., if via group-led programs or independent usage), and (2) *the physical activity level of users*.

Following the hybrid II design, we will evaluate the impact of the intervention and the potential contextual factors (community/organisational level factors) that may influence implementation (barriers/facilitators) of the TERM framework. In addition, we will evaluate older people’s quality of life, wellbeing and self-reported health care utilisation. The RE-AIM model [25] (see measures described in Table 3) and our logic model will guide the project evaluation (Fig. 1).

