##### AIM 2a –Physical activity level of older people users

We have already demonstrated that using the Seniors Exercise Parks improves physical function (objective measures), increases self-rated quality of life and wellbeing, reduces falls risk, and increases physical activity levels [17, 18]. ENJOY IMP-ACT aims to scale up this evidence-based program. We will conduct face-to-face intercept surveys with older people who utilise the equipment using the *self-reported physical activity* questionnaire from the Active Australia Survey (see below for more details) [38]. The survey assesses walking, moderate, and vigorous activity in the previous week, plus providing an indicator of total activity and meeting recommended physical activity guidelines. The Active Australia questions are valid, reliable and recommended for use in Australian population-based research. This will provide measures of time and frequency of physical activities and also identify any changes not likely to be attributable to the program (such as walking) [39], and provide a comparator to nationally representative data.

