##### AIM 2—evaluation of the ENJOY Seniors Exercise Park on physical activity and wellbeing

Summary statistics will be used to describe the demographic, socioeconomic, equipment usage and health-related characteristics of Seniors Exercise Park area users at each time point. Data will also be examined and reported relative to the adult general public, based on the distribution of age, marital status, and country of birth (using Australian Bureau of Statistics census data for each local government area). Linear and logistic regression models (with main effects for site, time-point, season and their interaction) will be used to examine the impact of the implementation intervention on physical activity level (primary outcome) and other health user characteristics. Statistical significance of the interaction term will be used to determine if the outcome varied between sites at each intervention time point (I1-I3) or M1 relative to their baseline difference.

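### The Aim 2 outcome concerns equipment users but survey eligibility does not require equipment use, and the stated model does not adjust for a change in who is surveyed

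*Protocol article*

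**What the plan says.** The Primary outcomes section names two primary measures; the second is "the physical activity level of users". The AIM 2a section agrees with it: "We will conduct face-to-face intercept surveys with older people who utilise the equipment".

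The operational sections are wider. Recruitment says: "Older people visiting the participating parks are potential participants for the intercept surveys and will be recruited at the sites". The inclusion rule for the survey is that "the following inclusion criteria will be applied: (1) adults aged 60 and over, (2) adults who are able to understand basic English", and the exclusion criteria are "1) participants who identify themselves as less than 60 years of age and (2) who are unable to understand basic conversational English". The Intercept surveys section says: "Potential participants (park users in the specified target area) will be approached by trained, clearly identifiable research staff".

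That section limits a person to one survey in the baseline and maintenance period but allows repeats during the intervention. No cohort is defined.

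For analysis, the AIM 2 section says: "Linear and logistic regression models (with main effects for site, time-point, season and their interaction) will be used to examine the impact". The impact in question is that of TERM on how active respondents are, which the section labels a primary outcome. Respondents' demographic, socioeconomic, usage and health characteristics are summarised at each time point and compared with census data. They are not named as model terms.

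**The concern.** Two weaknesses combine. First, the protocol does not settle whose activity is being measured: people who use the equipment, or older people who happen to be in the target area. Someone aged 60 or over sitting on a bench meets every stated survey criterion. Second, the analysis compares the mean activity of whoever was intercepted before TERM with that of whoever was intercepted during and after it. None of the stated terms describes the respondent.

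If the mix of respondents changes, that mean can move although no individual has changed. Drawing in inactive older people, which would be a success for the programme, could look like harm. Replacing passers-by with equipment users could look like benefit. This affects a co-primary outcome. It also carries into Aim 3, where the social return is modelled from before-and-after differences in the same intercept surveys.

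**Working it through.** **1. Who is to be surveyed.** Setting the sections side by side:

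| Section | Population |
|---|---|
| Study objectives, Aim 2 | Older people using the equipment |
| Primary outcomes | Users |
| AIM 2a | Older people who use the equipment |
| Sample size, intercept surveys | Built from 10 observed users of the Seniors Exercise Park |
| Recruitment | Older visitors to the parks |
| Inclusion and exclusion criteria | Age 60 or over, with basic English |
| Intercept surveys | Park users in the target area |
| Statistical analysis, AIM 2 | Users of the park area |

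The first four point to equipment users and the last four to visitors. The protocol knows the distinction: the observers code intended use separately from playing, looking or sitting. Those scans are anonymous, however, so the code is not attached to a survey respondent.

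**2. Whether the same people are compared.** The planned numbers reproduce:
- Baseline: 10 × 0.75 = 7.5, given as 8 per site.
- M1: 20 × 0.80 × 0.75 = 12 per site.
- I1–I3: 34 per site. The derivation is not given; (10 + 15 + 20) × 0.75 = 33.75 matches if growth runs 10, 15, 20, which is an assumption.
- Total: 8 + 34 + 12 = 54 per site; 54 × 6 = 324. Across six sites this is 48 at baseline, 204 in I1–I3 and 72 at M1.

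The 25% loss covers refusals and people who have already completed the survey. The article describes verbal consent and paper surveys, with no code linking one survey to the next. Largely different respondents before and after are therefore to be expected, although the overlap is not stated.

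**3. Whether the mix is expected to change.** The usage target foresees independent users rising from 10 to 20 and 30 users in organised classes. The Training section adds induction sessions that may serve clients referred by general practice or community health centres, including high-risk clients. A change in the kinds of user is thus part of the design.

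**4. What the model holds fixed.** Its terms are site, time-point, season and their interaction. Site and season do not identify visitor type. Age group, gender, postcode-based SEIFA and local residence are all collected in the survey but are not among the stated terms.

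**5. What follows.** Take two visitor types, A and B, with mean activity m_A and m_B, and let p be the share of type B among respondents. If nobody changes behaviour, the difference between periods is

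(p_after − p_before) × (m_B − m_A).

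The protocol gives neither the shares among respondents nor the difference in activity. The result may be positive, negative or zero. To show scale only, assume the share of equipment users among respondents rises by 30 to 40 points and the types differ by 0.2 to 0.5 SD:
- 0.30 × 0.2 = 0.06 and 0.40 × 0.2 = 0.08 SD
- 0.30 × 0.5 = 0.15 and 0.40 × 0.5 = 0.20 SD

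For comparison, the difference detectable with 48 against 204 respondents (assuming two-sided 5%, 80% power and independent responses) is (1.96 + 0.84) × √(1/48 + 1/204) = 2.80 × 0.160 = 0.45 SD. The illustrated artefact is 13% to 44% of that.

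**The case against.** The strongest reply is that the intention is clear enough: the AIM 2a section and the sample-size basis both refer to equipment users. This stands to the extent that a reader might infer that the protocol has decided to analyse non-users. It has not. It contradicts itself, and the remedy is to reconcile the sections.

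Second, the protocol has partial safeguards. Respondent characteristics, including equipment usage, are reported at each time point, so a shift in mix would be visible. The activity questionnaire is also meant to pick out changes, such as in walking, that are unlikely to be due to the programme. Both help, but seeing a shift does not remove it from the estimate, and a change in mix can move any component of activity.

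Third, the stated terms do not exclude further covariates, and a full list could sit in an analysis plan that is not shown. That is fair. Even so, the article names the terms for this primary outcome, and none describes the respondent.

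Three stronger inferences are tempting and are not supported:
- **That gender selection distorts the mix.** When several people are present, the choice of whom to approach "would be guided by aiming to overall recruit an equal number of men and women". This is an aim, not a quota. Applied throughout, it tends to steady the gender mix between periods.
- **That the usage target sizes the bias.** Thirty class users out of 50 is a target for observed use under Aim 1. The survey is sized separately, on at least a twofold increase, with no projected class share among respondents. Multiplying 60% by an assumed activity difference gives a figure the protocol does not support. Class and independent users are also both equipment users, so restricting the analysis to users would not remove that part.
- **That within-person change could carry the main conclusion.** With 8 baseline surveys per site, limits on repeat surveys and no linkage described, too few before-and-after pairs can be expected.

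**Conclusion.** The point holds in a limited form. The population of the co-primary physical activity outcome is stated inconsistently, and the stated model cannot separate a change in who is surveyed from a change in activity, yet its result is to be read as impact. The bias can go either way and may be nil. The protocol does not say how visitor types differ in activity or how the mix of respondents will move, so no size can be derived; the range of 0.06 to 0.20 SD rests wholly on assumed inputs. A reader might infer that a spurious effect will be reported; the documents support only that one can be. The change should be made, because it concerns a co-primary outcome and most of the information needed is already collected.

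**What to change.** - Reconcile the Recruitment, Inclusion criteria, Exclusion criteria, Intercept surveys and AIM 2 analysis sections with the Primary outcomes and AIM 2a sections, so that one population is named throughout.
- Record for each survey respondent whether they use the equipment and in what mode (independently or in an organised class).
- Define the Aim 2 primary analysis set as older equipment users, and report other visitors separately.
- Add age group, gender, SEIFA decile and local residence to the linear and logistic models, and report results by usage mode. The usage-mode results are needed because the mix of users can change even within the restricted set.
- Account for repeat respondents in the intervention phase where they can be identified.
- Word the result as a difference in activity level among the users surveyed in each period, not as change in individuals.

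The cost is one or two extra survey items, revised wording and a somewhat smaller primary set. Adjustment will reduce bias from the measured characteristics but cannot remove unmeasured self-selection, and the report should say so.
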